### 7.1. Statistical and Methodological Issues

The study protocol rests on a solid longitudinal design, contemplating repeated measurements of specific biomarkers over time. When dealing with an observational study of effectiveness and with LMM/GEE (see Statistical Analysis) having repeated measurements over time as dependent variables, the estimation of the sample size mainly depends on the number of potential confounders to be included in the models rather than on a predefined effect of the drug. In this case, a total of 640 observations over the time period are expected to be collected [i.e., 80 patients x four longitudinal visits including baseline (n = 320 observations) in the exposed group and 80 patients x four longitudinal visits including baseline (n = 320 observations) in the unexposed group]. This high number of observations will allow us to adjust the effect of Etelcalcetide versus calcitriol or vitamin D analogs on study endpoints for both baseline and longitudinal potential confounders, thus obtaining robust and precise effect estimates. Furthermore, linear mixed models and generalized estimating equations analyses are robust methods for dealing with various patterns of missingness, an issue of particular relevance in studies of comparative effectiveness. Furthermore, since this is not an interventional study, the observational nature of the protocol will be guaranteed by inviting treating nephrologists to tailor the appropriate dosage for each patient individually, aiming to reach the KDIGO PTH target level as in everyday clinical practice. In the group receiving Etelcalcetide, calcitriol may also be added as needed according to the standard clinical approach to address hypocalcemia.

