## 2. Methods

### 2.1. Study Design

This is a national, multi-center, comparative effectiveness, observational, longitudinal study with no predefined interference on drug dosing by the investigators. Nineteen Italian centers will be involved. In each center, 14 patients will be screened for eligibility and about 10–12 patients are scheduled to be enrolled. This study will enroll 160 hemodialysis patients (80 patients treated with Etelcalcetide and 80 age- and sex-matched patients treated with calcitriol or a vitamin D analog, paricalcitol) (Figure 1).

Given the observational nature of this study, the investigators will not recommend target goals of Etelcalcetide treatment. The treating nephrologists will tailor their target dose of Etelcalcetide on an individual-level patient basis in order to achieve the KDIGO PTH target levels. In the Etelcalcetide-treated group, the addition of calcitriol is allowed when required by current clinical practice (for correction of hypocalcemia). Blood samples for the measurement of specific biomarkers will be collected in concomitance with the routine blood sampling scheduled in each center. At baseline, all relevant demographic, clinical, and biochemical data will be collected in compliance with the privacy laws of the European Union. The study design is illustrated in Figure 2.

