### 4.2. Data Analysis

Normally distributed variables will be summarized as means and standard deviations, non-normally distributed variables as medians and interquartile ranges, and categorical data as absolute numbers and percentages. At baseline, the between-groups comparisons will be performed using the independent *t*-Test, the Mann–Whitney U Test, or the Chi-squared test, as appropriate. The between-groups comparisons of repeated measurements of biomarkers (as continuous variables) over time will be performed by linear mixed models (LMM) or generalized estimating equations (GEE). No imputation method of missing values will be applied. In these analyses, the effect of the exposure to Etelcalcetide in treated patients versus those untreated will be preliminarily investigated by including the group variable, the time, and the interaction term between the group variable and time. The effect of potential confounders on the effectiveness of Etelcalcetide on the study outcomes will be further investigated by adjusting for all potential confounders, including medications, by multiple regression models. Sensitivity analysis by applying the propensity score approach will be also performed. The primary analysis will be conducted considering the patients as belonging to the treatment arm they had at the beginning of observation. A secondary analysis will also be performed taking into account any cross-over. Survival analyses will be performed using the Kaplan–Meier and Cox regression methods. All statistical analyses will be performed using a standard statistical package (STATA 16, StataCorp. Stata Statistical Software. College Station, TX, USA).

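### Adjusting the starting-arm comparison for longitudinal covariates, with none of those the drug itself changes excluded, would not estimate the total effect on vitamin K-dependent proteins

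*Protocol article*

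**What the plan says.** Four statements in the protocol article bear on this.

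- **Timing of covariates (7.1).** The 640 observations are said to allow adjustment of the drug effect "on study endpoints for both baseline and longitudinal potential confounders, thus obtaining robust and precise effect estimates".
- **Content and method (4.2).** Confounding is handled by "adjusting for all potential confounders, including medications, by multiple regression models". Neither a covariate list nor the time at which medications are measured is given.
- **Contrast (4.2).** "The primary analysis will be conducted considering the patients as belonging to the treatment arm they had at the beginning of observation". Then: "A secondary analysis will also be performed taking into account any cross-over", with no method named.
- **Treatment after baseline (2.1).** "In the Etelcalcetide-treated group, the addition of calcitriol is allowed when required by current clinical practice", the reason being hypocalcemia.

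The main aim (section 1) is whether Etelcalcetide, compared with vitamin D or its analogs, raises vitamin K-dependent protein (VKDP) levels at 3, 9 and 18 months. That is a question about the total effect of the starting treatment.

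**The concern.** When exposure is fixed at the start, only what precedes treatment can confound it. A covariate measured later and altered by the drug lies downstream. Ordinary regression on such a covariate does two things: it takes out the share of the effect that passes through the covariate, and it links the arm to any unmeasured cause shared by covariate and outcome. The result is not the total effect. It is a valid direct effect only if no such unmeasured cause exists.

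At stake is the adjusted estimate for all four main outcomes (total MGP, dp-ucMGP, total BGP, ucBGP), which 7.1 presents as robust and precise. Section 7.3 names only unmeasured confounding as a remaining risk.

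**Working it through.** **1. The plan's own figure.** 80 patients × 4 visits = 320 per group, and 2 × 320 = 640 observations. This reproduces. It is a count of records and says nothing about which covariates may validly enter the model.

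**2. Which longitudinal covariates does the drug change, on the article's own account?**

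- PTH: the drug lowers its secretion (section 1), and its dose is titrated to a PTH target (2.1).
- Calcium: hypocalcemia is reported as a side effect (section 7).
- Calcitriol: it is added in the Etelcalcetide group to correct hypocalcemia (2.1, 7.1). Calcitriol or an analog also defines the comparison group (2.1, 3.3). As a time-varying medication covariate it would therefore be part of the contrast and, in exposed patients, a response to treatment.

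No section removes these from the adjustment set or names a method for time-varying covariates affected by treatment.

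**3. What adjustment does, in a linear illustration.** Every parameter here is assumed. There are 160 patients, 80 per arm (A), and three post-baseline visits. L is a baseline covariate that differs by 0.3 between arms. U is an unmeasured cause.

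- Covariate: M = aA + 0.5L + uU + error (SD 0.8)
- Outcome: Y = dA + bM + 0.3L + uU + patient effect + error
- Total effect of arm: d + ab
- Expected arm coefficient given L only: d + ab
- Expected arm coefficient given L and M: d − a·u²/(u² + 0.8²)

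With u = 0 the last line is d, so the mediated part ab is lost. With u = 0.5, u²/(u² + 0.64) = 0.25/0.89 = 0.281. The collider term is then +0.14 for a = −0.5 and +0.28 for a = −1.

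Means of 400 simulated datasets per row, by pooled linear regression. The L-only column is for u = 0, except in the two d = 0 rows, where u = 0.5:

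| d | a | b | True total | L only | L and M, u = 0 | L and M, u = 0.5 (formula) |
|---|---|---|---|---|---|---|
| 0.25 | −0.5 | −0.25 | 0.375 | 0.38 | 0.25 | 0.39 (0.39) |
| 0.25 | −0.5 | −0.5 | 0.50 | 0.49 | 0.24 | 0.38 (0.39) |
| 0.25 | −1.0 | −0.25 | 0.50 | 0.51 | 0.26 | 0.53 (0.53) |
| 0.25 | −1.0 | −0.5 | 0.75 | 0.75 | 0.26 | 0.51 (0.53) |
| 0 | −0.5 | 0 | 0 | 0.00 | – | 0.13 (0.14) |
| 0 | −1.0 | 0 | 0 | 0.01 | – | 0.29 (0.28) |

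With u = 0 the loss runs from (0.375 − 0.25)/0.375 = 33% to (0.75 − 0.25)/0.75 = 67%. With u = 0.5 the estimate falls above or below the truth, and a null effect becomes non-null. If U acted on M and Y in opposite directions, the collider term would change sign.

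**4. Limits of the illustration.** Arm is independent of U given L, so adjustment for L recovers the truth by construction. A non-randomised study has no such assurance. Pooled regression corresponds to a GEE with independence working correlation and no group-by-time term, so the planned models would give somewhat different numbers. The mechanism would be the same.

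**The case against.** The strongest reply is that the harmful model is nowhere written down.

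- No section lists post-baseline PTH, calcium or calcitriol as covariates. Section 3.2 lists calcium and PTH as outcome measures.
- The reference to longitudinal covariates stands in 7.1, a passage defending the sample size, and does not say which analysis it serves. It could mean the cross-over analysis, where time-varying covariates matter.
- The model specification is in 4.2, which gives medications no timing, so baseline medication is a possible reading. A covariate list can properly be left to a fuller document.
- Other estimates are planned. The drug effect "will be preliminarily investigated by including the group variable, the time, and the interaction term between the group variable and time", and a propensity score sensitivity analysis follows.
- The Abstract mentions an effect beyond PTH lowering, which might justify adjusting for PTH.

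Much of this stands. A reader might infer that the primary model will certainly contain post-baseline PTH, calcium and add-on calcitriol, and that the main result will be wrong by a known amount. The documents support neither inference.

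What does not fall away is the stated rule. Taken together, 7.1 and 4.2 license adjustment for longitudinal variables and for all potential confounders without excluding those the drug changes, and an analysis plan that follows them inherits the problem. The group-by-time model is called preliminary and is unadjusted for confounders. The propensity score analysis is a sensitivity analysis only. The Abstract offers the effect beyond PTH as a suggestion from earlier data, whereas the stated aim concerns the total effect.

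**Conclusion.** The point holds as a fault in the stated adjustment rule. If post-initiation covariates changed by Etelcalcetide enter the starting-arm LMM or GEE, the coefficient is not the total effect on VKDPs. PTH, calcium and add-on calcitriol are such covariates on the article's own description. Longitudinal covariates that the drug does not change would not cause this bias.

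Size and direction cannot be derived from the documents. They depend on the mediated share, on how strongly the drug moves the covariate, and on unmeasured common causes, none of which is given. The losses of one third to two thirds and the spurious effects of 0.13 to 0.29 show what can happen under the assumed values and are not forecasts for this study.

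**What to change.** - **7.1:** for the primary starting-arm analysis, strike the words *and longitudinal* from the description of the adjustment.
- **4.2:** state that confounders and medications in that model are pre-treatment values. An enrolment value is not always one, because 3.3 and 3.4 admit patients who have been on Etelcalcetide for up to 1 month. For them, use values from before initiation where available.
- **Effect beyond PTH:** report any model adjusting for post-baseline PTH, calcium or medications as a separately labelled mediation analysis with its assumptions stated.
- **Cross-over secondary analysis (4.2):** name a method suited to time-varying covariates affected by treatment, for example inverse-probability weighting, instead of entering them in the outcome model.

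The cost is wording, some retrieval of pre-initiation values from existing records, and a weighted secondary analysis. The sample size is unchanged. The primary model gives up the reduction in residual variance that post-baseline covariates would bring.

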### 7.2. Dissemination Plan

The target audience to disseminate the results of the ETERNITY-ITA study includes healthcare professionals (nephrologists, endocrinologists, and general practitioners), patients suffering from chronic kidney disease and related conditions, pharmaceutical companies involved in the production of Etelcalcetide and calcitriol, and policy-makers and regulatory bodies involved in healthcare decision-making. The dissemination channels include scientific journals, national and international meetings, and online platforms such as ResearchGate, LinkedIn, and professional forums.

### 7.3. Limitations

As an observational study of comparative effectiveness, ETERNITY-ITA can provide valuable insights into how treatments perform in real-world settings. However, the observational design comes with limitations that can affect the reliability and validity of the findings, such as those due to confounding. However, such problems will be minimized by collecting data and adjusting for major potential confounders that may interfere with the pathway between treatments and outcome variables. Notwithstanding such an approach aimed at controlling for confounding variables, it is not possible to completely exclude that there may be unmeasured confounders that remain unaccounted for, leading to residual confounding and potentially biased estimates of treatment effects.

## 8. Conclusions

The clinical remarkable significance of this study is to provide first-time data on the ability of Etelcalcetide in real life to prevent increased VKDP levels, alone or in association with other vascular bone markers, such as skeletal fragility and vascular calcifications, in hemodialysis patients, with a resulting decrease in morbidity and mortality.

## Figures and Tables

**Figure 1 jcm-13-05888-f001:**
[figure not shown]
Study groups.

**Figure 2 jcm-13-05888-f002:**
[figure not shown]
Graphical representation of the study protocol.

## Data Availability

Data are contained within the article.
